### 2.2.3. 11C-METOMIDATE PET-CT

For the FAS, whether dexamethasone was taken for 3-5 days prior to the scan will be summarised; where this has not occurred, the reasons will be summarised and/or listed.

For the FAS, the following laboratory measures will be summarised as a whole, and in relation to whether the 11C-Metomidate PET-CT results indicated BAH, unilateral APA (left), unilateral APA (right), or were inconclusive:

- Sodium, potassium, creatinine, eGFR, urea, bicarbonate, renin mass, renin activity, aldosterone, aldosterone renin ratio (ARR), serum cortisol, serum ACTH

For the FAS, the following 11C-Metomidate PET-CT measures will be summarised as a whole, and in relation to whether the results indicated BAH, unilateral APA (left), unilateral APA (right), or were inconclusive:

- Right Adrenal
  - Number of possible tumours
  - Mean tumour diameter
  - Maximum standardised uptake value (SUVmax) over all tumours, (calculated by TOF and SharpIR)
  - SUVmax over the normal adrenal (TOF and SharpIR)
  - Ratio of SUVmax over tumour to SUVmax over normal adrenal (TOF)
  - Ratio of SUVmax over tumour to SUVmax over normal adrenal (SharpIR)
  - Probability of adrenal adenoma
- Left Adrenal
  - Number of possible tumours
  - Mean tumour diameter
  - Maximum standardised uptake value (SUVmax) over all tumours, (calculated by TOF and SharpIR)
  - SUVmax over the normal adrenal (TOF and SharpIR)
  - Ratio of SUVmax over tumour to SUVmax over normal adrenal (TOF)
  - Ratio of SUVmax over tumour to SUVmax over normal adrenal (SharpIR)
  - Probability of adrenal adenoma
- SUVmax over liver (TOF and SharpIR)
- Overall Probability of Unilateral Aldosterone Producing Adenoma

For the Substudy Population, these same measures will be summarised for scans performed whilst taking spironolactone, and when off spironolactone. Bland-Altman plots and cross-tabulations will be used to assess the level of agreement between scans.

## 2.2.4. PARTICIPANT CHARACTERISTICS AT BASELINE

The following information collected at baseline (after study scans have been completed) will be summarised for all participants in the Full Analysis Set, and in the Substudy Population; for those in the FAS, data will be presented according to whether the participant later underwent surgical treatment:

- Medications
  - Number of different classes of antihypertensive medications being used, and whether using each class of medication
  - Total defined daily doses of antihypertensive medications being used, and defined daily doses of each class of medication
- Clinic readings of systolic blood pressure, diastolic blood pressure, heart rate
- Home readings of systolic blood pressure, diastolic blood pressure, heart rate (mean of all available readings; minimum 6 readings required)
- ECG
  - presence of atrial fibrillation, and U-wave abnormalities
- Blood biomarkers
  - Sodium, potassium, magnesium, creatinine, eGFR, urea, bicarbonate, troponin, brain natriuretic peptide, renin mass, renin activity, aldosterone, aldosterone renin ratio (ARR)
- 24-hour urine biomarkers
  - Sodium, potassium
- Spironolactone/Eplerenone therapy
- Quality of life
  - SF36
    - Physical functioning
    - Role limitations due to physical health
    - Role limitations due to emotional problems
    - Energy or fatigue
    - Emotional wellbeing
    - Social functioning
    - Pain
    - General health
    - Health change
  - Hospital Anxiety and Depression (HAD)
    - Depression
    - Anxiety
    - Total
  - Perceived Stress Score
  - Pittsburgh Sleep Quality Index
  - Fatigue Symptom Inventory
    - Level of Fatigue on Most Fatigued Day
    - Level of Fatigue on Least Fatigued Day
    - Level of Fatigue on Average
    - Level of Fatigue Now

- Days Fatigued in Week
- How Much of Day Spent Fatigued
- Pattern of Fatigue
- Disruption Index

### **2.2.5. WEEK 2**

The following information collected at 2 weeks will be summarised for all participants in the Full Analysis Set, as a whole and according to whether the participant later underwent surgical treatment:

- Medications
  - Number of different classes of antihypertensive medications being used, and whether using each class of medication
  - Total defined daily doses of antihypertensive medications being used, and defined daily doses of each class of medication
- Clinic readings of systolic blood pressure, diastolic blood pressure, heart rate
- Home readings of systolic blood pressure, diastolic blood pressure, heart rate
- Blood biomarkers
  - Sodium, potassium, creatinine, eGFR, urea, bicarbonate
- Spironolactone/Eplerenone therapy

### **2.2.6. WEEK 4**

The following information collected at 4 weeks will be summarised for all participants in the Full Analysis Set, as a whole and according to whether the participant later underwent surgical treatment:

- Medications
  - Number of different classes of antihypertensive medications being used, and whether using each class of medication
  - Total defined daily doses of antihypertensive medications being used, and defined daily doses of each class of medication
- Clinic readings of systolic blood pressure, diastolic blood pressure, heart rate
- Home readings of systolic blood pressure, diastolic blood pressure, heart rate
- Blood biomarkers
  - Sodium, potassium, creatinine, eGFR, urea, bicarbonate

### **2.2.7. MDT DECISION**

MDT decisions (proceed to surgery, or medical management) will be summarised in relation to the diagnosis (BAH, APA, or inconclusive) from each test modality, and combinations of test results (see Section 1.5).

**2.2.8. SURGERY**

The following information, regarding surgery, will be summarised for those participants who undergo surgery:

- Location of surgery (left/right)
- Method of surgery (open/laparoscopic)
- Number of adenomas/nodules
- Whether immunohistochemistry was performed
  - if yes, results for CYP11B1, CYP11B2, KCNJ5, and NPNT (negative/+ /++ /+++)
- Presence of hyperplasia in the normal (adjacent) adrenal

For all adenomas/nodules, the following data will be summarised:

- Size (mm)
- Cell type
- CYP11B1, CYP11B2, KCNJ5, and NPNT (negative/+ /++ /+++)
- Somatic mutation (KCNJ5/ATP1A/ATP2B3/CTNNB1/CACNAID/CDM1/Not Performed/Other)

**2.2.9. 4 WEEKS POST-SURGERY**

The following information, collected 4 weeks after surgery, will be summarised for those participants who undergo surgery:

- Medications
  - Number of different classes of antihypertensive medications being used, and whether using each class of medication
  - Total defined daily doses of antihypertensive medications being used, and defined daily doses of each class of medication
- Clinic readings of systolic blood pressure, diastolic blood pressure, heart rate
- Home readings of systolic blood pressure, diastolic blood pressure, heart rate
- Blood biomarkers
  - Sodium, potassium, creatinine, eGFR, urea, bicarbonate, renin mass, renin activity, aldosterone, aldosterone renin ratio (ARR)

**2.2.10. 3 MONTHS POST-SURGERY**

The following information, collected 3 months after surgery, will be summarised for those participants who undergo surgery:

- Medications
  - Number of different classes of antihypertensive medications being used, and whether using each class of medication
  - Total defined daily doses of antihypertensive medications being used, and defined daily doses of each class of medication

- Clinic readings of systolic blood pressure, diastolic blood pressure, heart rate
- Home readings of systolic blood pressure, diastolic blood pressure, heart rate
- Blood biomarkers
  - Sodium, potassium, creatinine, eGFR, urea, bicarbonate, renin mass, renin activity, aldosterone, aldosterone renin ratio (ARR)

#### **2.2.11. 6 MONTHS POST-SURGERY / 9-12 MONTHS POST-MDT DECISION**

The following information, collected 6 months after surgery, or 9-12 months after the MDT decision, will be summarised for those all participants and in relation to whether they underwent surgery:

- Medications
  - Number of different classes of antihypertensive medications being used, and whether using each class of medication
  - Total defined daily doses of antihypertensive medications being used, and defined daily doses of each class of medication
- Clinic readings of systolic blood pressure, diastolic blood pressure, heart rate
- Home readings of systolic blood pressure, diastolic blood pressure, heart rate
- ECG
  - presence of atrial fibrillation, and U-wave abnormalities
- Blood biomarkers
  - Sodium, potassium, magnesium, creatinine, eGFR, urea, bicarbonate, troponin, brain natriuretic peptide, renin mass, renin activity, aldosterone, aldosterone renin ratio (ARR)
- Cardiac Magnetic Resonance imaging
  - whether performed
- Quality of Life
  - SF36
    - Physical functioning
    - Role limitations due to physical health
    - Role limitations due to emotional problems
    - Energy or fatigue
    - Emotional wellbeing
    - Social functioning
    - Pain
    - General health
    - Health change
  - Hospital Anxiety and Depression (HAD)
    - Depression
    - Anxiety
    - Total
  - Perceived Stress Score

- Pittsburgh Sleep Quality Index
- Fatigue Symptom Inventory
  - Level of Fatigue on Most Fatigued Day
  - Level of Fatigue on Least Fatigued Day
  - Level of Fatigue on Average
  - Level of Fatigue Now
  - Days Fatigued in Week
  - How Much of Day Spent Fatigued
  - Pattern of Fatigue
  - Disruption Index

### **2.2.12. 12 MONTHS POST-SURGERY**

The following information, collected 12 months after surgery, will be summarised for those participants who undergo surgery:

- Medications
  - Number of different classes of antihypertensive medications being used, and whether using each class of medication
  - Total defined daily doses of antihypertensive medications being used, and defined daily doses of each class of medication
- Clinic readings of systolic blood pressure, diastolic blood pressure, heart rate
- Home readings of systolic blood pressure, diastolic blood pressure, heart rate
- Blood biomarkers
  - Sodium, potassium, creatinine, eGFR, urea, bicarbonate, renin mass, renin activity, aldosterone, aldosterone renin ratio (ARR)

### **2.2.13. 24 MONTHS POST-SURGERY / POST-MDT DECISION**

The following information, collected 24 months after surgery / MDT decision, will be summarised for those all participants and in relation to whether they underwent surgery:

- Medications
  - Number of different classes of antihypertensive medications being used, and whether using each class of medication
  - Total defined daily doses of antihypertensive medications being used, and defined daily doses of each class of medication
- Clinic readings of systolic blood pressure, diastolic blood pressure, heart rate
- Home readings of systolic blood pressure, diastolic blood pressure, heart rate
- Blood biomarkers
  - Sodium, potassium, creatinine, eGFR, urea, bicarbonate, renin mass, renin activity, aldosterone, aldosterone renin ratio (ARR)

## **2.3. EFFICACY OUTCOMES**

### **2.3.1. PRIMARY OUTCOMES**

The primary outcomes will be analysed hierarchically. If the first primary analysis is statistically significant at  $p < 0.05$ , then the second primary outcome will be analysed; if the second primary analysis is statistically significant at  $p < 0.05$ , then the second primary outcome will be analysed; and so on. If any primary analysis fails to reach  $p < 0.05$ , then subsequent analyses will be considered secondary analyses.

Each primary outcome will be analysed in the subgroup of FAS patients who undergo surgery.

- Cure of hypertension at 6 months (non-inferiority analyses)
  - comparing accuracy of AVS and 11C-Metomidate PET-CT
  - each scan judged to be accurate if it indicated unilateral disease and cure of hypertension was achieved after surgery, or if the scan did not indicate unilateral disease and cure was not achieved after surgery
  - report estimated difference in accuracy (Newcombe-Wilson method for paired data) between 11C-Metomidate PET-CT and AVS, with 95% CI
  - non inferiority of 11C-Metomidate PET-CT will be declared if the lower limit of the above 95% CI is greater than -17%
  - each measure of cure (see Section 1.8) will be analysed in turn
- Cure of hypertension at 6 months (superiority analyses)
  - in addition to above, report p-value from exact McNemar test
  - superiority of 11C-Metomidate PET-CT will be declared if  $p < 0.05$ , and the lower limit of the 95% CI is greater than 0%

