## **11.0 Diagnostic Investigations**

The primary control intervention is AVS and will be performed according to an identical protocol

at all centres whose internal audit data indicate a successful bilateral cannulation rate of >75%. Briefly, the femoral vein is cannulated under local anaesthesia and catheters advanced under fluoroscopic guidance into each adrenal vein.(17) The procedure is performed under conditions of ACTH stimulation, which facilitates unequivocal confirmation of secure adrenal vein cannulation. Blood samples from both adrenal veins and the lower part of the inferior vena cava are analysed for aldosterone (A) and cortisol (C) and an aldosterone/cortisol (A/C) ratio calculated at each site. Lateralisation (providing evidence for an adrenalectomy to be recommended) is deemed to exist if the A/C value in one adrenal vein is at least 4-fold higher than the other. In preparation for AVS, treatment to control blood pressure is limited to a non-dihydropyridine calcium antagonist (e.g. verapamil) and doxazosin (together with potassium supplementation as needed), as the treatments least likely to interfere with interpretation of aldosterone/renin measurements. Although some rise in blood pressure is permitted in preparation for AVS, severely hypertensive patients may require additional therapy according to clinical judgement.

The experimental intervention is  $^{11}\text{C}$ -metomidate PET-CT. There has been no change in the protocol used since the proof-of-concept study. Patients are treated with dexamethasone 0.5 mg 6-hourly for 3 days, then receive an injection of 250 mBq (on average) of  $^{11}\text{C}$ -metomidate, with CT and PET scanning of the adrenal area 20-30 minutes later. A positive (lateralization) result is indicated by a maximum standardised uptake at least 25% greater in one adrenal gland compared to the other.

The assessment of the two diagnostic modalities will be undertaken at a monthly MDT of endocrinologists and radiologists. Patients will be offered surgery if one or both techniques indicate unilateral disease. For the very small number of cases (we estimate 1 in 25 on the basis of the proof-of-concept study), where AVS and  $^{11}\text{C}$ -metomidate PET-CT each meet these criteria for lateralisation, but to opposite sides, we will defer to the Trial Steering Committee (TSC) (see section 11).

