### **33.0 CALCULATION OF PROPOSED SAMPLE SIZE**

The table below shows potential outcomes from the two separate investigations in patients recruited to MATCH:

| Diagnostic Tests |                | Normalisation of plasma renin & aldosterone/renin ratio after surgery (i.e. confirmed unilateral PHA) |            |
|-------------------------|----------------|------------------------------------------------------------------------------------------------------------------|------------|
| AVS              | PET-CT  | No                                                                                                        | Yes |
| Unsuccessful            | Bilateral      | A (=9%)                                                                                                          | B (=0%)    |
| Unsuccessful            | Unilateral     | C (=1%)                                                                                                          | D (=10%)   |
| Bilateral               | Bilateral      | E (=35%)                                                                                                         | F (=0%)    |
| Bilateral               | Unilateral     | G (=1%)                                                                                                          | H (=9%)    |
| Unilateral              | Bilateral      | I (=0.5%)                                                                                                        | J (=3.5%)  |
| Unilateral (c)          | Unilateral     | K (=1%)                                                                                                          | L (=29%)   |
| Unilateral (d)          | Unilateral     | M (=0.25%)                                                                                                       | O (=0.25%) |
| Unilateral              | Unilateral (d) | P (=0.25%)                                                                                                       | Q (=0.25%) |

**Key:** c = concordant; D = discordant (i.e. PET-CT and AVS lateralise to opposite sides)

The accuracy of PET CT will be estimated in patients having surgery, given by:

$$(D+H+I+L+O+Q) / n$$

The accuracy of AVS will be estimated by  $(G+J+L+M+P) / n$

A test of whether these accuracies differ will therefore be a test of whether

$$(D+H+I+L+O+Q) = (G+J+L+M+P)$$

or whether

$$(D+H+I+O+Q) = (G+J+M+P)$$

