This can be achieved by a one sample binomial test of whether

$$p = (D+H+I+O+Q) / (D+H+I+G+J+M+O+P+Q) = 50\%$$

Given the estimated proportions given above, the anticipated value of p is 80%. To have 90% power at a 1% significance level to show that p is different to 50%, assuming the true value of p to be 80%, we require the number of participants in the subgroup

$(A+D+H+I+G+J+M+O+P+Q)$  to be 32 (based on an exact binomial test). Since this subgroup is an estimated 25% of the study population, we would need to recruit 128 participants

Assuming missing data of 10% of people recruited, our target recruitment will be 140. This original sample size calculation assumed that 50% of patients would proceed to medical therapy, and 50% to surgery. In the light of an observed asymmetry between these two group sizes, the total sample will be increased to 165.”

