### **1.5. SAMPLE SIZE AND POWER**

The original sample size calculations carried out at the design stage are reported in section 33.0 of the study protocol, and is reproduced below:

The table below shows potential outcomes from the two separate investigations in patients recruited to MATCH:

| Diagnostic Tests |                | Normalisation of plasma renin & aldosterone/renin ratio after surgery (i.e. confirmed unilateral PHA) |            |
|------------------|----------------|-------------------------------------------------------------------------------------------------------|------------|
| AVS              | PET-CT         | No                                                                                                    | Yes        |
| Unsuccessful     | Bilateral      | A (=9%)                                                                                               | B (=0%)    |
| Unsuccessful     | Unilateral     | C (=1%)                                                                                               | D (=10%)   |
| Bilateral        | Bilateral      | E (=35%)                                                                                              | F (=0%)    |
| Bilateral        | Unilateral     | G (=1%)                                                                                               | H (=9%)    |
| Unilateral       | Bilateral      | I (=0.5%)                                                                                             | J (=3.5%)  |
| Unilateral (c)   | Unilateral     | K (=1%)                                                                                               | L (=29%)   |
| Unilateral (d)   | Unilateral     | M (=0.25%)                                                                                            | O (=0.25%) |
| Unilateral       | Unilateral (d) | P (=0.25%)                                                                                            | Q (=0.25%) |

Key: c = concordant; D = discordant (i.e. PET-CT and AVS lateralise to opposite sides)

The accuracy of PET CT will be estimated in patients having surgery, given by:

$$(D+H+I+L+O+Q) / n$$

The accuracy of AVS will be estimated by  $(G+J+L+M+P) / n$

A test of whether these accuracies differ will therefore be a test of whether

$$(D+H+I+L+O+Q) = (G+J+L+M+P)$$

or whether

$$(D+H+I+O+Q) = (G+J+M+P)$$

This can be achieved by a one sample binomial test of whether

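### The SAP 2.3.1 accuracy rule has no side match and credits a failed AVS when PET-guided surgery fails; the effect is small on the planning table but grows as cure becomes rarer

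*Combined protocol and SAP*

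**What the plan says.** SAP 2.3.1 sets the analysis set: "Each primary outcome will be analysed in the subgroup of FAS patients who undergo surgery". Its accuracy rule has two limbs. The first covers a positive test: "each scan judged to be accurate if it indicated unilateral disease and cure of hypertension was achieved after surgery". The second covers a test that was not positive: "or if the scan did not indicate unilateral disease and cure was not achieved after surgery". Neither limb mentions side. The second limb does not separate a bilateral result from a test that gave no result. The rule is applied in turn to the four PASO-based outcomes of SAP 1.8.1, from at least partial biochemical success to complete clinical success.

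Protocol section 33 works from a table of test results against biochemical normalisation after surgery. It takes PET accuracy as (D+H+I+L+O+Q)/n. "The accuracy of AVS will be estimated by" (G+J+L+M+P)/n. Cell C (AVS unsuccessful, PET unilateral, not normalised) earns neither test credit. Cells M, O, P and Q are the opposite-side cases, which the key calls "discordant (i.e. PET-CT and AVS lateralise to opposite sides"), and all four enter the binomial test of p. SAP 1.5 reproduces this: "The original sample size calculations carried out at the design stage are reported in section 33.0 of the study protocol".

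SAP 1.10.3 says in general terms that its analyses differ from the protocol. SAP 1.10.4 names only 18F-CETO and the PASO outcomes. SAP 2.3.6 repeats the primary analyses without technical AVS failures.

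**The concern.** The primary estimand is the difference in accuracy between PET-CT and AVS, so the scoring rule defines it.

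First, if the tests lateralise to opposite glands, both indicate unilateral disease. Both are scored accurate after cure and both inaccurate after failure. The plainest disagreement the tests can have becomes a concordant pair, and a test that pointed to the wrong gland can be called correct.

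Second, an unsuccessful AVS did not indicate unilateral disease. If surgery guided by PET alone then fails, AVS scores as accurate although it gave no answer. That adds a discordant pair in favour of AVS.

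The SAP thus carries two incompatible definitions of accuracy, in 1.5 and 2.3.1. The difference between them bears on a non-inferiority decision with a 17-point margin.

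**Working it through.** **Inputs.** Section 33 cells, in % of recruits: C 1, D 10, G 1, H 9, I 0.5, J 3.5, K 1, L 29, and M, O, P, Q 0.25 each. Operated patients (at least one test unilateral) sum to 56. Normalised among them: D+H+J+L+O+Q = 52, and 52/56 = 93%. Margin: -17 points (SAP 2.3.1). Operated number: 70 (section 23; the synopsis says 90).

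**The plan's own figure.** D+H+I+O+Q = 20. Adding G+J+M+P = 5 gives 25. So p = 20/25 = 80%, matching "the anticipated value of p is 80"%. With n = 32 and rejection at 23 or more, the exact one-sided level is 0.0100 and power is 91%; 32/0.25 = 128. The figure reproduces at a one-sided 1% level.

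**Where the rules differ.** They differ in five cells only:

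| Cell | SAP 2.3.1 credits | Section 33 credits |
|---|---|---|
| C | AVS | neither |
| O, Q | both | PET only |
| M, P | neither | AVS only |

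**Planning table.**
- Section 33: PET 49/56 = 87.5%; AVS 34/56 = 60.7%; difference 26.8 points.
- SAP rule: PET 49/56 = 87.5%; AVS (C+G+J+L+O+Q) 35/56 = 62.5%; difference 25.0 points.
- The 1.8-point gap is cell C (1/56). The opposite-side cells cancel because all four are equal.
- With 70 operated, non-inferiority probability is above 99.9% either way. Exact McNemar power (two-sided 0.05) is 87% under the SAP rule and 92% under the formula.

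**Failed-AVS credit when cure is rarer (stress test).** Assume one cure rate c in every operated stratum. Strata: AVS failed and PET unilateral f = 11/56 (19.6%); AVS bilateral and PET unilateral b = 10/56; AVS unilateral and PET bilateral a = 4/56. The remaining 31/56 are scored alike.
- PET only accurate: (f+b)c + a(1-c).
- AVS only accurate, with the credit: ac + (f+b)(1-c). Without it: ac + b(1-c).
- The credit is therefore f(1-c). At c = 0.5 it is 5.5/56 = 9.8 points.

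| Cure rate | Credit to AVS | Difference with / without credit | Non-inferiority probability with / without (70 operated) |
|---|---|---|---|
| 90% | 2.0 | 24.3 / 26.3 | >99.9% / >99.9% |
| 70% | 5.9 | 12.1 / 18.0 | 96% / 99.9% |
| 50% | 9.8 | 0.0 / 9.8 | 59% / 97% |

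The probabilities are simulated with the Newcombe paired 95% interval. Protocol 4.3 expects at least 50% of the additional surgical patients to be cured of hypertension. The 50% row is thus relevant to complete clinical success, not to the biochemical outcomes.

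**Side.** Under the SAP rule the opposite-side rows add nothing to the difference, because both tests score alike. On the planning table the difference is (D+H+I) - (C+G+J) = 19.5 - 5.5 = 14, and 14/56 = 25.0 points. With side matching, a share s operated on PET's side at success rate q adds s(2q-1); on AVS's side it subtracts the same.
- Table values (s = 1, q = 0.5): no change.
- s = 1, q = 0.9, all on one test's side: (14 ± 0.8)/56 = 23.6 to 26.4.
- Section 11 puts such cases higher ("we estimate 1 in 25 on the basis of the proof-of-concept study"). Taking that as 4% of recruits, all operated, the denominator is 59 and the side-blind difference is 14/59 = 23.7. At q = 0.9, all on one test's side gives (14 ± 3.2)/59 = 18.3 to 29.2, about 5.4 points either way. An even split stays at 23.7.

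**The case against.** The strongest reply is that the rule asks whether a test would have sent the patient to surgery. On that view a failed AVS and a bilateral AVS have the same consequence; protocol 4.2 says many patients with non-diagnostic AVS go no further. The hierarchy starts with biochemical success, where the planning figures show almost no effect. SAP 1.10.3 discloses that analyses differ, SAP 1.5 presents the formula as design history, and SAP 2.3.6 removes AVS failures. Opposite-side cases are few, are deferred to the Trial Steering Committee, and leave the analysis set if not operated.

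Much of this stands on size. It does not settle the text. A decision-based rule still needs the side, because pointing to the wrong gland is a wrong decision. SAP 2.3.6 does not address side. It also drops cell D, which only PET is credited for, so the planning difference becomes (39-34)/45 = 11.1 points, which answers a different question. The change in scoring is not among the deviations listed.

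Four stronger readings do not hold:
- That the rule could produce a false claim for PET through failed AVS. That credit favours AVS, so it works against PET in both tests.
- That both defects remove disagreements from the McNemar test. Only the side defect does; the failed-AVS credit adds discordant pairs.
- That the side defect biases the comparison in a known direction. It depends on which side is operated and how often surgery succeeds.
- That the protocol formula is a finished standard. Crediting O and Q to PET, and M and P to AVS, fits only if surgery followed PET in both rows, which section 33 does not say. Its table has a row for unsuccessful AVS but none for the equivocal zone described in protocol 4.2, so it gives no basis for scoring equivocal results as never accurate.

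**Conclusion.** The point holds: the rule is wrong on side and departs, unlisted, from the plan's own formula on failed AVS. On the planning assumptions the cost is 1.8 points of accuracy difference and about 5 points of superiority power, and the non-inferiority conclusion is unaffected. It becomes material for the later clinical outcomes if cure is much rarer than 93%. The 5.9 and 9.8 points, and the 59% against 97%, rest on a single cure rate whatever the tests showed and on 19.6% of operated patients having a failed AVS. They are stress cases, not forecasts. The side effect ranges from 0 at the table's values to about 5.4 points either way at the extreme.

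**What to change.** In SAP 2.3.1, score a test as accurate if it lateralised to the side removed and success was achieved, or if it gave a diagnostic result that did not lateralise to that side and success was not achieved. Score a technically unsuccessful AVS as not accurate, consistent with cell C, and keep the SAP 2.3.6 analysis. State before analysis how a technically successful but equivocal AVS is scored, since section 33 does not cover it. Define the O/Q and M/P credit in section 33 by the operated side, reconcile the 1% and 1-in-25 frequencies, and list the scoring change in SAP 1.10.4.

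On the planning table the new rule gives PET 49/56 and AVS 34/56, a difference of 26.8 points.

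The cost is wording and a few lines of code: side of surgery (SAP 2.2.8) and side by each test (SAP 2.2.2 and 2.2.3) are already collected. The downside is that the failed-AVS change moves results toward PET, so it should be made before outcomes are seen.
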